#### Algorithm-based care for depression (ABCD)

We adapted an ABCD antidepressant prescription model. ABCD is a resource-efficient, task-sharing model for delivering high quality, effective, safe antidepressant management in non-psychiatric settings. ABCD equips non-specialists (e.g., primary care clinicians or HIV clinicians) to safely and effectively prescribe and monitor antidepressants. The model trains staff to know what to measure (e.g., depressive severity, side effects, adherence), how and when to measure it, how to interpret the results, and what resulting course of action to pursue (e.g., maintain dose, increase dose, address side effects, switch medication). Key features include (1) treatment decisions guided by regularly measured metrics of depressive severity, side effects, and adherence; (2) an algorithm summarizing best-practices care based on metrics; (3) a treatment goal of remission (full resolution of symptoms); (4) low starting dose followed by dose adjustments until remission, as long as the medication remains tolerable; (5) ensuring an adequate trial (six to eight weeks at moderate to high dose); and (6) regular structured supervision for continuous quality improvement.

In our program, a patient initiates an antidepressant when identified with moderate to severe depressive severity (PHQ-9 score ≥ 10) combined with clinical confirmation of the presence of depression (Fig. 2). Every four weeks at the monthly ART appointment, considered critical decision points (CDPs), the patient reports depressive severity and side effects using standardized measures. These metrics guide a recommendation to increase, maintain, or decrease the antidepressant dose or to change treatments. If the patient is tolerating the medication but depressive symptoms have not remitted, a dose increase is recommended. If side effects are not tolerable, the recommendation is to address them or switch treatment. At CDP3 (i.e., after 12 weeks), the patient has either achieved remission (and enters a maintenance phase) or has demonstrated treatment resistance to the current medication (and receives a new treatment plan).

**Fig. 2 Fig2:**
[figure not shown]
Algorithm-based care for depression (ABCD) Timeline

ABCD has proven to be effective in primary care [41, 42] and in HIV care [30, 43] in high-income countries, and more recently has demonstrated safety, feasibility, and acceptability when adapted for HIV care and delivered by a general practice medical providers in Cameroon, Tanzania and Uganda [34, 44, 45].

#### .Friendship bench problem-solving therapy (PST)

We adapted a PST intervention developed for use in Zimbabwe called the Friendship Bench [38]. PST is a psychological treatment that focuses on teaching patients how to identify triggers and effectively manage stressful life events by learning or reactivating problem solving skills [46]. PST evolved from social problem solving theory, framing three sequential phases for addressing problems including (1) discovery (identifying solution), (2) performance (implementing solution), and (3) verification (assessing outcome) [47]. The goal-oriented approach is a cognitive-behavioral intervention focused on improving an individual’s coping abilities through psychoeducation, interactive problem-solving exercises, and developing action plans aimed at reducing psychological distress. PST is easy to learn, has been integrated successfully into primary care settings [48], and is an effective strategy for depression management [49–51].

The original Friendship Bench consisted of task-shifting PST to lay health workers in Zimbabwe; requiring minimal training with structured supervision. The Friendship Bench PST intervention resulted in clinically meaningful improvement in mental health outcomes [38] and was highly acceptable among patients with perceived positive benefits [52, 53]. Other studies from SSA have confirmed the feasibility and effectiveness of PST for management of common mental disorders, including depression [54, 55].

In our program, the developers of the ‘Friendship Bench’ conducted a training for trainers who then went on to train a team of community health workers stationed at each clinic to deliver PST. The program built structures at both clinics for holding Friendship Bench PST sessions. Additionally, we staffed one Friendship Bench counsellor at each clinic throughout the duration of the program.

#### Combined intervention

Our intervention combined ABCD and PST into a stepped-care intervention with clinical response appropriate to the level of depressive severity (Fig. 3). Patients scoring 0–4 on the PHQ-9, indicating no depression, receive no intervention. Patients scoring 5–9 on the PHQ-9, indicating mild depressive symptoms, receive Friendship Bench PST. Patients scoring ≥10 on the PHQ-9, indicating moderate to severe depressive symptoms, are offered ABCD as the first treatment option, since literature indicates that medications and counselling are equally effective for this group and medication management can be offered more efficiently as first-line within existing clinical care. For this group, Friendship Bench PST is an alternative or augmentation option for those who do not tolerate or do not respond to antidepressant treatment. In all cases, ART providers continue to monitor patients’ depressive severity at follow-up visits with the option of modifying their treatment plan if their symptoms worsen or do not improve after three months of an adequate treatment course.

**Fig. 3 Fig3:**
[figure not shown]
Program Design

### Setting

We are conducting the evaluation study at two public-sector primary care HIV clinics in Lilongwe, Malawi: Area 18 and Area 25 health clinics. These clinics are managed by Lilongwe District Health Office. More detailed description of the study setting has been published elsewhere.

### Population and sample size

We are abstracting screening data for all consenting adult (≥18 years old) patients newly initiating ART and screened for depression at the time of ART initiation at the study sites during the study period. Additional depression treatment and outcome data are being abstracted for all patients who screen positive for mild, moderate, or severe depressive symptoms (PHQ-9 total score ≥ 5) [56, 57].

We focused on two populations of interest. For the primary population of interest, all patients with depressive symptoms (PHQ-9 score ≥ 5), the original sample size was determined to provide 80% power to detect an 11 percentage point pre-post difference in the primary outcome. For the secondary (smaller) population of interest, all patients with moderate to severe depression (PHQ-9 score ≥ 10), the original sample size would provide the same power to detect an 18 percentage point pre-post difference. To achieve this power, we would require 645 patients with any depressive symptoms and 225 patients with moderate to severe depressive symptoms.

Based upon the historical rate of new ART patients (122 per month between the two clinics) and the expected prevalence of any depressive symptoms (35%) and moderate to severe depressive symptoms (12%) based on prior literature [58] [7], we originally planned for a 15-month data collection period to accrue the targeted sample. During the course of data collection, the rate of new ART patients was higher than expected but the prevalence of depressive symptoms was lower than expected. After extending the recruitment period for an additional 5 months, the accrual of new ART patients concluded with a final sample of 2084 individuals. The prevalence of mild to severe depression was 24.1% (*n* = 502) and the prevalence of moderate to severe depression was 6.3% (*n* = 131). This sample has 80% power to detect a slightly larger difference in the primary outcome of 12 percentage points (e.g. 60% vs. 72%) or a risk ratio of 1.2 for those with mild to severe depression. For those with moderate to severe depression, the sample has 80% power to detect an improvement in the primary outcome of 22 percentage points (e.g. 60% vs. 82%) or a risk ratio of 1.4.

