### Data analysis

The primary program evaluation question is whether the depression treatment program results in improved HIV and mental health outcomes for patients with HIV and depression relative to the standard of care prior to program implementation. The main analysis will follow an “intent-to-treat” approach, classifying patients according to screening vs. treatment phase (unexposed vs. exposed to the program) without regard to actual treatment received. In our main analysis, we will define our primary outcome, retention in HIV care with viral suppression 6 months after starting ART, as never being more than 30 days late to any scheduled return visit in the first 6 months on ART and having a viral load < 1000 copies/mL at 6 months; patients not retained or not suppressed will be coded as a failure. (Table 2**)** This composite outcome was chosen as the primary outcome because it is the definition of ART clinical success in the Malawian ART treatment system; those not retained and those retained but not suppressed are both clinical failures. This main analysis will estimate the probability of retention and viral suppression 6 months after starting ART using a generalized linear model with binomial error distribution, adjusting for calendar time and potential confounders that are imbalanced between arms at baseline, potentially including age, sex, clinic, PHQ-9 score, and presence of suicidal ideation. We will model these associations using separate generalized linear models among two samples: (a) those with mild, moderate, or severe depression (PHQ-9 ≥ 5) and (b) those with moderate to severe depression (PHQ-9 ≥ 10).

**Table 2 Tab2:** Outcome Variables

	Definition	Type
Primary Outcome		
Retention with Viral Suppression	both attending all ART appointments “on time” through 6 months and having a viral load < 1000 copies/mL at 6 months	Binary
Secondary Outcomes		
Viral Suppression	viral load < 1000 copies/mL at 6 months	Binary
Retention	attending all ART appointments “on time” through 6 months	Binary
	number of ART appointments attended through 6 months	Count
Consistent ART supply	Never going more then 5 days without ART, as calculated from pills dispensed and time between attended appointments	Binary
Depression Remission	PHQ-9 Score < 5 at 6 months	Binary

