### Timeline

The screening phase began at Clinic A in April 2017 and Clinic B in May 2017. The treatment phase was integrated into Clinic A after 7 months, in November 2017, and into Clinic B after 11 months, in April 2018. Identification of new patients concluded at both clinics in November 2018. Follow-up data abstraction is expected to continue through June 2019.

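### The stated 80% power (12 points for n = 502, 22 points for n = 131) is that of an unadjusted comparison; under the planned calendar-time adjustment it is below 50%, and about 36–39% with linear time

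*Protocol article*

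**What the plan says.** The protocol article's section on population and sample size gives power for the final sample. For PHQ-9 ≥ 5 (502 patients): "This sample has 80% power to detect a slightly larger difference in the primary outcome of 12 percentage points (e.g. 60% vs. 72". For PHQ-9 ≥ 10 (131 patients): "the sample has 80% power to detect an improvement in the primary outcome of 22 percentage points", illustrated as 60% against 82%. The section mentions no time adjustment, clinic term, variance inflation or split between phases.

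The data analysis section specifies the main model for the same outcome as "using a generalized linear model with binomial error distribution, adjusting for calendar time and potential confounders that are imbalanced between arms at baseline". As worded, calendar time is always in the model. Clinic is on a list of covariates that may enter if imbalanced. The model is fitted separately in the two severity samples.

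The timeline section sets out the calendar: "The treatment phase was integrated into Clinic A after 7 months, in November 2017, and into Clinic B after 11 months, in April 2018". Screening had started in April 2017 at clinic A and one month later at clinic B, and accrual stopped at both in November 2018.

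**The concern.** Quoting unadjusted power for an adjusted analysis does little harm when the covariates are roughly unrelated to exposure. Here the adjusting variable largely determines exposure. Within each clinic every exposed patient starts ART after every unexposed one, so only the staggered launch and the assumed shape of the time trend separate the program effect from time.

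The published 80% sets how readers will weigh the result. If power for 12 points is below one half, a non-significant estimate says little against an effect of that size, yet the stated figure suggests that it says a good deal. The article expects the findings to inform practice and policy on integrating depression care.

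**Working it through.** **Inputs.** From the article: N = 502 and 131; 60% vs 72% and 60% vs 82%; the calendar above. Assumed, because not stated: two-sided alpha 0.05; uniform accrual within clinic; clinic A holding a share a = 35–65% of patients; no true secular trend.

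**Phase split.** Clinic A has 7 screening and 13 treatment months of 20; clinic B has 11 and 8 of 19. The treated fraction is f = a × 13/20 + (1 − a) × 8/19, which is 0.50, 0.54 and 0.57 for a = 0.35, 0.50 and 0.65. The clinics are in different phases from November 2017 to March 2018, which is 5 of 20 months.

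**Step 1: reproduce the stated figure.** Power = Φ[(|p1 − p0| − 1.96 × SE0) / SE1], with SE0 from the pooled proportion and SE1 from the separate proportions. With a = 0.50 there are 269 treated and 233 untreated patients, and the pooled proportion is 0.664:
- SE0 = √[0.664 × 0.336 × (1/233 + 1/269)] = 0.0423
- SE1 = √[0.24/233 + 0.2016/269] = 0.0422
- Power = Φ[(0.12 − 0.0828)/0.0422] = Φ(0.88) = 81%

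The same formula gives 80% for 131 patients at 60% vs 82%. An even split between phases gives 81.2% and 79.9%. The article's 80% is therefore the power of a simple comparison of independent patients.

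**Step 2: how much of phase does time explain?** Number the months from April 2017 = 0 and take a = 0.50. Mean start month is 13.98 in the treatment phase and 4.87 in the screening phase, and the variance of start month is 31.7. Then R² = f(1 − f) × (difference in means)² / variance = 0.249 × 9.11² / 31.7 = 0.65, a correlation of about 0.81. Adding clinic raises R² to about 0.72.

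**Step 3: power under adjustment.** The variance of the phase effect is multiplied by VIF = 1/(1 − R²). For linear time with a = 0.50, VIF = 2.87, so both standard errors grow by √2.87 = 1.69, to 0.0716 and 0.0715. Power = Φ[(0.12 − 0.1403)/0.0715] = Φ(−0.28) = 39%. The effective sample is 502/2.87 = 175.

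Ranges below are over a = 35–65%. Detectable differences (80% power) start from 60%.

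| Time term | VIF | Power, 12 points, n = 502 | Power, 22 points, n = 131 | Detectable, n = 502 | Detectable, n = 131 |
|---|---|---|---|---|---|
| None | 1 | 81% | 80% | 12 | 22 |
| Calendar year only | 2.2–2.3 | 46–49% | 45–47% | 17–18 | 30–31 |
| Linear | 2.9–3.0 | 38–39% | 36–38% | 19–20 | 34–35 |
| Linear + clinic | 3.5–3.7 | 31–33% | 30–32% | 21–22 | 36–37 |
| Month indicators + clinic | 5.3–5.9 | 21–24% | 20–23% | 25–27 | not attainable |

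**Step 4: check by simulation.** The VIF approach is approximate for a binomial model. Simulated logistic models (1,500 runs per scenario) gave, for n = 502, 80–83% unadjusted, 37–39% with linear time and 30–33% with linear time plus clinic. For n = 131 they gave 79–82%, 34–36% and 28–30%. The approximation is, if anything, slightly generous in the smaller sample.

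**The case against.** The strongest reply is that the article's arithmetic is right for what it computes. The original target was described as a pre-post contrast: "the original sample size was determined to provide 80% power to detect an 11 percentage point pre-post difference in the primary outcome". The rates are given only as examples, and a journal article leaves the form of the time term to the analysis plan. Accrual has also closed, so the power statement no longer sets the sample size, and a time-adjusted confidence interval will show the imprecision whatever the power paragraph says.

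Much of this stands. There is no slip of arithmetic, the form of time may properly be specified elsewhere, and neither the estimate nor its interval is affected. That a null result would be misread is a risk; the article makes no such claim. But the sentences on the final sample refer to a difference in the primary outcome, for which the article names one main model, and that model includes calendar time. None of the time terms tried brings power above about 50%, so leaving the form open does not rescue 80%.

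A reader might infer several stronger points that the documents do not support:
- *That power is simply about 30%, or that PHQ-9 ≥ 10 needs about 96% success.* Both require clinic in the model, which the article makes conditional on imbalance. With linear time alone, power is 36–39% and the PHQ-9 ≥ 10 sample needs about 94%.
- *That phase and time are nearly collinear.* R² is about 0.65–0.73 with linear time. The five-month stagger is the design's means of separating the two, and it does so in part.
- *That clustering by clinic and month makes the test invalid.* The article gives no intraclass correlation, so any figure rests on an assumed one. At an assumed 0.01, simulated type I error was 6.4%, against 6–7% with clustered standard errors, which shows no gain.
- *That separate models by severity are an error.* They are a legitimate choice. One pooled model would gain precision but must assume the same secular trend across severity levels.

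**Conclusion.** The concern holds as a mismatch between the power statement and the planned analysis. The stated 80% belongs to an unadjusted pre-post comparison that assumes no secular trend. Under the calendar-time adjustment the article commits to, power at the stated differences is about 36–39% with linear time, the mildest reading with a continuous trend. It is lower with clinic or month terms and about 45–49% with a coarse calendar-year term. With linear time the planned analysis would therefore miss a true effect of the stated size at least six times in ten.

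These figures rest on two-sided 0.05, uniform accrual within clinic, a clinic A share of 35–65% and the 60% reference rate. The actual phase split and clinic shares will move them somewhat. It would take a VIF near 1 to restore 80%, and the calendar does not allow that for the time terms examined.

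**What to change.** Restate both power figures as differences detectable with 80% power under the calendar-time-adjusted model. State with them the assumed form of calendar time, whether clinic is in the model, and the phase split by clinic, which can now be counted from the accrued sample. On the assumptions used here the entries would be about 19–20 points (linear time), 21–22 (plus clinic) or 25–27 (month indicators plus clinic) for PHQ-9 ≥ 5, and about 34–37 points or not attainable for PHQ-9 ≥ 10. Add one sentence saying that 12 and 22 points apply only to an unadjusted pre-post comparison that assumes no secular trend.

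The cost is a short recalculation and new wording, with no new patients and no change to the planned model. The drawback is a less favourable stated figure, most visibly for the PHQ-9 ≥ 10 sample. Clustered standard errors and a pooled severity model are options for the authors to weigh; this point does not require them.

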### Data abstraction and management

Data on viral loads, HIV appointment attendance, and depressive symptoms is abstracted from electronic and paper medical records and the depression treatment registry at the sites. ART appointment data including the date of the appointment, the expected return date, and medication prescribed is recorded in the EMR, on a paper patient file (called an HIV Mastercard), or both. The results of the viral load tests are recorded in the EMR. Data on patients’ depressive symptoms and depression treatment are only recorded on paper in an additional patient filed attached to the ART mastercard (called a mental health mastercard). The community health workers responsible for administering the Friendship Bench problem-solving therapy also maintain paper records (called a Counselling Mastercard) that capture engagement with the PST sessions. Cost information was collected using a time-audit approach to estimate costs of delivering the program, including the opportunity cost of training participation and the time providers and supervisors spend to deliver and supervise the program. Time-audit data was captured through a combination of direct observation of medical provider and counsellor encounters supplemented with self-reporting by counsellors.

### Data analysis

The primary program evaluation question is whether the depression treatment program results in improved HIV and mental health outcomes for patients with HIV and depression relative to the standard of care prior to program implementation. The main analysis will follow an “intent-to-treat” approach, classifying patients according to screening vs. treatment phase (unexposed vs. exposed to the program) without regard to actual treatment received. In our main analysis, we will define our primary outcome, retention in HIV care with viral suppression 6 months after starting ART, as never being more than 30 days late to any scheduled return visit in the first 6 months on ART and having a viral load < 1000 copies/mL at 6 months; patients not retained or not suppressed will be coded as a failure. (Table 2**)** This composite outcome was chosen as the primary outcome because it is the definition of ART clinical success in the Malawian ART treatment system; those not retained and those retained but not suppressed are both clinical failures. This main analysis will estimate the probability of retention and viral suppression 6 months after starting ART using a generalized linear model with binomial error distribution, adjusting for calendar time and potential confounders that are imbalanced between arms at baseline, potentially including age, sex, clinic, PHQ-9 score, and presence of suicidal ideation. We will model these associations using separate generalized linear models among two samples: (a) those with mild, moderate, or severe depression (PHQ-9 ≥ 5) and (b) those with moderate to severe depression (PHQ-9 ≥ 10).

**Table 2 Tab2:** Outcome Variables

	Definition	Type
Primary Outcome		
Retention with Viral Suppression	both attending all ART appointments “on time” through 6 months and having a viral load < 1000 copies/mL at 6 months	Binary
Secondary Outcomes		
Viral Suppression	viral load < 1000 copies/mL at 6 months	Binary
Retention	attending all ART appointments “on time” through 6 months	Binary
	number of ART appointments attended through 6 months	Count
Consistent ART supply	Never going more then 5 days without ART, as calculated from pills dispensed and time between attended appointments	Binary
Depression Remission	PHQ-9 Score < 5 at 6 months	Binary

In secondary analyses, we will consider ART care retention through 6 months (binary), number of ART appointments attended in the first 6 months (count), maintaining consistent ART supply through 6 months (binary), and viral suppression at 6 months among those retained (binary). Further, secondary analyses will take an “as treated” approach, comparing patients who receive treatment in the treatment phase to all patients during the screening phase; and an “as adequately treated” approach, comparing patients who receive adequate treatment (≥3 consecutive months of protocol-concordant antidepressant prescriptions or ≥ 4 counseling sessions) during the treatment phase to all patients during the screening phase. Data are not available on antidepressant adherence. (Table 3).

**Table 3 Tab3:** Analyses

Analysis	Definition
Primary: “intent-to-treat”	Initiated after program launch
“as treated”	Received depression treatment
“as adequately treated”	≥3 consecutive months of protocol-concordant antidepressant prescriptions or ≥ 4 counselling sessions

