### Study design

The study employs a multiple baseline evaluation design in two clinics to evaluate the impact of the integrated depression treatment program on HIV outcomes (Fig. 1). The reasons for the choice of the study design has been described published elsewhere [39].

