### Intervention program

We integrated depression screening and treatment into ART care into two clinics in Lilongwe, Malawi using a multiple baseline design in two phases: a screening phase and a treatment phase.

During the screening phase, HIV care providers screened patients for depression and monitored their depressive symptoms using the Patient Health Questionnaire-9 (PHQ-9). HIV care providers managed patients identified with depression according to existing care pathways, which included: 1) counselling by the HIV care provider; 2) referral to an on-site or off-site psychiatric nurse or other mental health specialist; or 3) in acute cases, transport to the outpatient psychiatric unit at the nearby district hospital.

At the launch of the treatment phase, HIV care providers were trained in algorithm-guided antidepressant management [38]; additionally, clinic-based lay health workers completed training in the Friendship Bench problem-solving therapy counselling protocol [38]. During this phase, providers are continuing to screen patients for depression. The providers manage cases of depression identified during the treatment phase with either antidepressants or problem-solving therapy, and providers monitor their depression treatment response at follow-up visits.

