## Discussion

This novel pilot program is Malawi’s first depression treatment program for people living with HIV and one of the few in the sub-Saharan Africa region to use a task-shifting model to provide both problem-solving therapy and antidepressant depression treatment [34–38]. This study will be the first to evaluate the impact of such a program on both mental health and HIV outcomes and to investigate the potential benefits of this task-shifting depression care model. Findings from this study will directly inform the Malawi Ministry of Health’s ongoing national strategic plans on mental health.

The study design draws both from implementation science and epidemiologic methods, with the ultimate goal of generating evidence-based practices, interventions and policies that can readily (and rapidly) be adopted and integrated into routine care in public sector settings [59–61]. We have conscientiously designed the evaluation to yield high quality, real-world findings on integrating depression management into HIV care that are readily applicable to the implementation of integrated mental health services in non-specialist settings.

The program itself focuses on provider training to manage antidepressants and provide evidence-based counselling, and thus cannot be randomized at the individual level. Since patients do not see the same provider from one appointment to the next, in this context the intervention could not be randomized at the provider level either. A cluster-randomized trial was also beyond the resources available for this project. Given these constraints, a multiple baselines design provides stronger causal inference than would be available with a simple pre-post design. Multiple baseline designs have been advocated as one of the designs providing the strongest causal inference apart from the randomized trial [62].

We anticipate that the study will generate evidence on the effect of depression management on HIV outcomes and the feasibility of integrating depression management into existing HIV care clinics. The results of the study will inform practice and policy decisions on integration of depression management in HIV care clinics in Malawi and similar low-income country settings, allowing design of a scale up strategy.

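### The primary model and the final-sample power figures make no stated allowance for clinic-by-month correlation, although exposure is set by clinic and start month; if such correlation remains after adjustment, standard errors are too small.

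*Protocol article*

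**What the plan says.** The Study design section states: "The study employs a multiple baseline evaluation design in two clinics". Under Timeline, "The screening phase began at Clinic A in April 2017 and Clinic B in May 2017"; Clinic A moved to the treatment phase in November 2017, Clinic B in April 2018, and identification of new patients ended at both in November 2018. The switch applies to the whole clinic: "At the launch of the treatment phase, HIV care providers were trained in algorithm-guided antidepressant management" (Intervention program). The Discussion explains that the programme works through provider training "and thus cannot be randomized at the individual level".

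The Data analysis section defines exposure by "classifying patients according to screening vs. treatment phase (unexposed vs. exposed to the program) without regard to actual treatment received". The primary outcome, retention with viral suppression at 6 months, is modelled "using a generalized linear model with binomial error distribution". On covariates, the plan speaks of "adjusting for calendar time and potential confounders that are imbalanced between arms at baseline". The candidates for that second group are worded only as "potentially including age, sex, clinic, PHQ-9 score, and presence of suicidal ideation". Calendar time is therefore definite, though its functional form is not given, and clinic is optional. The article mentions no random effect, GEE, robust variance, overdispersion term or ICC.

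The Population and sample size section claims 80% power for 60% versus 72% with 502 patients, and for 60% versus 82% with 131 patients.

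**The concern.** Phase is essentially constant within a clinic-month, so the programme effect is estimated from differences between groups of patients, while the named model takes its variance from individuals. The primary outcome depends on attending every scheduled ART visit, usually monthly, at the clinic and on having a viral load at 6 months. The Discussion says that patients do not see the same provider from one appointment to the next, so the clinic is the shared unit of care. A disruption in one clinic in one period would move the outcomes of many patients together.

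Plain binomial variance has no term for this. If such variation remains after adjustment, confidence intervals are too narrow and the primary test rejects too often. With two clinics, a clinic-specific disturbance near a switch month is a leading rival explanation for a programme effect, and the article says the results will inform policy.

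**Working it through.** **Inputs.**
- Clinic-months (Timeline): Clinic A, April 2017 to November 2018, 20 months; Clinic B, May 2017 to November 2018, 19 months; total 39. Screening 7 + 11 = 18; treatment 13 + 8 = 21.
- Primary sample (Population and sample size): 502, so m = 502/39 = 12.9 patients per clinic-month.
- Assumed: two-sided alpha of 0.05 (not stated), equal split between phases, ICC from 0 to 0.05 (none given).

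**Step 1: reproduce the stated power.** Two-proportion test, 251 per phase, 60% versus 72%, mean 66%:
- pooled SE = sqrt(2 × 0.66 × 0.34 / 251) = 0.0423
- unpooled SE = sqrt((0.60 × 0.40 + 0.72 × 0.28) / 251) = 0.0419
- power = Phi((0.12 − 1.96 × 0.0423) / 0.0419) = 81.2%

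Treatment-to-screening ratios of 1.25, 1.5 and 0.67 give 80.9%, 79.9% and 79.4%. For 131 patients and 60% versus 82%, an equal split gives 79.9%. At an equal split, 80% power for 12 points needs 488 independent patients, so 502 leaves room for a design effect of only 502/488 = 1.03. The final-sample figures thus contain essentially no allowance for clustering. The original targets (645 and 225) are less informative, because no baseline rate is stated for them.

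**Step 2: effect of clinic-month correlation.** Design effect DE = 1 + (m − 1) × ICC; interval width multiplies by sqrt(DE); effective N = 502/DE; type I error = 2 × (1 − Phi(1.96/sqrt(DE))).

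| ICC (assumed) | DE | Interval width | Effective N | Power, 12 points | Type I error |
|---|---|---|---|---|---|
| 0 | 1.00 | 1.00 | 502 | 81.2% | 5.0% |
| 0.01 | 1.12 | 1.06 | 449 | 76.7% | 6.4% |
| 0.02 | 1.24 | 1.11 | 406 | 72.4% | 7.8% |
| 0.05 | 1.59 | 1.26 | 315 | 61.4% | 12.1% |

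**Step 3: does the planned adjustment remove it?** The logit GLM was simulated on the 39 clinic-months with even accrual, 66% success, no programme effect and 2000 runs per setting (Monte Carlo error about ±1 point at 5%). Type I error with model-based standard errors:
- Shocks specific to a clinic-month, ICC 0 / 0.01 / 0.02 / 0.05: with clinic and linear time, 4.6% / 6.2% / 7.0% / 11.9%; with clinic and month indicators, 5.5% / 6.3% / 9.0% / 12.4%.
- Shocks common to both clinics, ICC 0.01 / 0.02 / 0.05: unadjusted, 7.0% / 8.9% / 15.6%; with clinic and linear time, 5.7% / 6.6% / 8.3%; with clinic and month indicators, 5.1% / 5.8% / 5.6%.

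The adjustment deals with common shocks, fully so only with a flexible time term. It does not deal with clinic-specific ones.

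**Step 4: does the remedy work?** In a separate simulation with clinic and linear time, clinic-month robust errors brought type I error at ICC 0.05 from 11.4% to 5.4%. When shocks were spread over overlapping 6-month outcome windows, the same remedy reduced it only from 19.2% to 12.7%, because correlation then crosses start months.

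**Power after adjustment.** Even at ICC 0, adjusting for clinic and time raised the simulated log-odds standard error of exposure from 0.19 to 0.36 (linear time) or 0.45 (month indicators). The powers in Step 2 precede that loss, which is larger than the loss from clustering in this range.

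**The case against.** The strongest reply is that a binomial GLM fixes a mean model and an error family, not a variance estimator. It is compatible with robust or clustered standard errors, which an article may leave to an analysis plan that is not shown. This stands in part. A reader might infer that the plan assumes independence outright or rules out a clustered variance; the article says neither. What keeps the point alive is that the published power figures for the final sample leave no room for clustering, and that clinic, which a two-clinic staggered design needs in the model, is only a possible covariate.

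Second, calendar time is a definite covariate, and some plausible shocks are common to both clinics: viral loads are tested at one hospital (Measures) and one district health office manages both clinics (Setting). This stands, and Step 3 confirms it. Only residual clinic-by-month variation is at issue.

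Third, the harm depends on an ICC that the documents do not give. At zero nothing changes, and at 0.01 the excess is about one percentage point. This stands, so it would go too far to say that the standard errors are too small as a matter of fact.

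Fourth, launches are given by month only, so exposure may be mixed within the two switch months. This has little bearing on the argument.

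**Conclusion.** The point holds conditionally. Exposure varies by clinic and start month, the named primary model has no term for variation at that level, and the power for the final sample reproduces under independence. If clinic-specific monthly variation remains after adjustment for time and clinic, the primary standard errors are too small. Over assumed ICCs of 0 to 0.05, type I error runs from about 5% to 12% and power for 12 points from about 81% to 61%, the latter before the cost of time adjustment. These figures assume even accrual, an equal split for the power calculation, and shocks independent between months; the overlapping-window simulation shows that type I error can be higher when they are not. The documents do not show that such variation is present, so the finding concerns what the plan should guard against. It merits a change of moderate priority.

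**What to change.** - Include clinic as a fixed effect in every primary model, with calendar time, whatever the baseline balance.
- Name the variance method: a clinic-month random intercept, or clinic-month cluster-robust standard errors with a small-sample correction. Two clinics are too few to cluster at clinic level. The correction matters more with a flexible time term: linear time leaves 39 − 4 = 35 clinic-month degrees of freedom, and month indicators leave 39 − 22 = 17 (20 months, clinic and exposure).
- Add a sensitivity analysis that allows correlation between neighbouring start months within a clinic, for example an autoregressive clinic-month effect, because the 6-month outcome windows overlap.
- State that inference is conditional on these two clinics and that the quoted power assumes no clustering.

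This costs a few lines of model specification and no further data. Intervals would be wider by about 6%, 11% or 26% at assumed ICCs of 0.01, 0.02 or 0.05, and essentially unchanged at an ICC of 0.
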